### Diagnostic methods of frailty and sarcopenia

Various tools are employed for diagnosing frailty, including the “frailty phenotype,” which assesses weakness, slowness, exhaustion, low physical activity levels, and weight loss. Pre-frailty is recognized with the presence of one or two of these criteria, while frailty requires three or more [11, 12]. Other diagnostic approaches include the Frailty Index, Clinical Frailty Scale, or FRAIL scale [13].

Sarcopenia diagnosis hinges on low muscle strength, reduced muscle quantity/quality, and diminished physical abilities. Probable sarcopenia is diagnosed if the first criterion is met, sarcopenia if both the first and second are present, and severe sarcopenia if all three criteria are satisfied [14]. Additionally, assessment tools such as SARC-F questionnaires, muscle strength tests, diagnostic procedures like dual-energy X-ray absorptiometry (DXA), or physical assessments such as gait speed tests are employed [14].

DXA imaging allows quick determination of muscle tissue quantity, setting thresholds at <5.5 kg/m^2^ for women and <7.23 kg/m^2^ for men, with minimal radiation exposure and lower costs compared to computed tomography. However, DXA's efficacy is limited by low specificity and inability to assess muscle quality regarding fatty infiltration [15]. Computed tomography is the gold standard for evaluating muscle mass and quality but carries risks due to radiation exposure [15].

Ultrasound has emerged as a promising tool for diagnosing muscle conditions like frailty and sarcopenia, demonstrating comparable efficacy to DXA in assessing muscle mass and excellent reliability (ICC >0.9). Analysis of echo intensity in ultrasound images allows inference of muscle tissue quality [16]. The International Society of Physical Medicine and Rehabilitation has proposed an ultrasound-based algorithm for evaluating muscle mass, utilizing muscle thickness relative to body mass index, with loss of body mass defined as values <1 for women and <1.4 for men when comparing past and current measurements [16].

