### Statistical analysis

The R program version 4.3.1 will be used for statistical analysis. The level of significance will be set at *p* < 0.05. The distribution of quantitative variables, both baseline and outcome, will be tested with the Kolmogorov-Smirnov test with Lilliefors correction. Qualitative variables will be described in absolute values and frequencies and quantitative variables with mean and standard deviation.

Baseline and outcome variables differences using Barthel Index (BI) score dichotomized between dependent (BI < 60) and independent (BI > 60) patients [31] using *T*-test or U-Mann-Whitney for quantitative variables (depending on their distribution) and Fisher exact test for qualitative variables.

A multivariate analysis will be performed with a machine learning model through principal analysis using logistic regression, applying the model to 75% of the subjects and evaluating its accuracy in the remaining 25%, with the objective of creating a trained model that allows the development of therapeutic intervention plans that enable both the evaluation and treatment of patients. Model will be controlled by baseline variables with significant differences in univariate analysis.

Model will be constructed with dichotomized Barthel index as dependent variable and manual grip strength, EuroQoL-5D, NPRS, cross sectional area and thickness of the rectus femoris, STAI, TSK and BDI as explanatory variable. Logistic model will be selected instead of others used in machine learning (e.g. Random Forest, Support Vector Machines or Gradient Boosting) because it is computationally more efficient and faster and more easily interpretable.

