### Sample characterization

Sociodemographic information (such as age, gender, level of education, perceived financial status, and frequency of social activity participation) is gathered using self-administered questionnaires as predictors of physical activity and fall history. These questionnaires are detailed in this paper.

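### The main model leaves sex to a univariate significance screen, although the protocol reads muscle quantity against different limits for women and men

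*Protocol article*

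**What the plan says.** - **Predictors.** Statistical analysis lists "manual grip strength, EuroQoL-5D, NPRS, cross sectional area and thickness of the rectus femoris, STAI, TSK and BDI as explanatory variable". Sample size calculation repeats the list. That is eight variables, without sex and with no index or scaling stated.
- **Outcome.** The Barthel Index is "dichotomized between dependent (BI < 60) and independent (BI > 60) patients".
- **Covariates.** "Model will be controlled by baseline variables with significant differences in univariate analysis", and "The level of significance will be set at *p* < 0.05". The same section then applies elastic net selection and reports variable importance.
- **Sex is available.** Sample characterization collects "Sociodemographic information (such as age, gender, level of education" and further items.
- **BMI.** Implications and limitations plans a BMI adjustment, because subcutaneous fat affects image clarity. It does not mention sex.
- **Sex-specific limits.** Diagnostic methods of frailty and sarcopenia describes an ultrasound algorithm "utilizing muscle thickness relative to body mass index, with loss of body mass defined as values <1 for women and <1.4 for men", and DXA "setting thresholds at <5.5 kg/m^2^ for women and <7.23 kg/m^2^ for men".

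**The concern.** The background treats muscle quantity as something whose meaning depends on sex. The model fits one pooled slope to thickness and one to area, and secures no term that separates a small muscle from being a woman. Part of the spread in the pooled measure is then the difference between men and women. If that part does not predict dependence, it dilutes the slope.

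The covariate rule does not reliably prevent this, because it asks whether sex alone is associated with the Barthel split. Sex can be unrelated to the outcome marginally and still be needed once muscle size is in the model. At stake are the ultrasound coefficients and the variable-importance ranking, which are central to the study's aim. Both could understate what ultrasound contributes.

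**Working it through.** **1. The plan's own figure.** Sample size calculation uses 100 + 50 × number of explanatory variables. With the eight listed, 100 + 50 × 8 = 500, which is the stated sample. Sex is therefore not counted in it.

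**2. What the limits show.** The ratios of male to female limits are 1.4 / 1.0 = 1.40 (BMI-relative thickness) and 7.23 / 5.5 = 1.31 (DXA). A BMI-relative thickness of 1.2, or any value from 1.0 to just under 1.4, is low for a man and not low for a woman. At equal BMI the same holds for thickness itself. The article gives no limit for rectus femoris area or grip strength.

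**3. Attenuation if sex is left out.** Suppose dependence follows only the deviation from the own-sex mean. For a single predictor on a linear scale:

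pooled slope / within-sex slope = SD² / (SD² + p(1 − p)d²)

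Here SD is the within-sex standard deviation, p the proportion of women and d the sex gap in means. None of these is in the article. Assumed: d = 0.4 (the gap between the two ultrasound limits, so d² = 0.16), SD 0.3 to 0.5, p 0.5 to 0.8.

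| p | SD | Calculation | Ratio |
|---|---|---|---|
| 0.5 | 0.3 | 0.09 / (0.09 + 0.04) | 0.69 |
| 0.5 | 0.5 | 0.25 / (0.25 + 0.04) | 0.86 |
| 0.8 | 0.3 | 0.09 / (0.09 + 0.0256) | 0.78 |
| 0.8 | 0.5 | 0.25 / (0.25 + 0.0256) | 0.91 |

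The share of predictor variance due to sex is one minus the ratio, so 9% to 31%.

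**4. Does the screen bring sex in?** This was simulated with n = 500 and 400 replicates per setting. Assumptions: 50%, 65% or 75% women; SD 0.3, 0.4 or 0.5; each sex centred on its own limit (1.0 and 1.4); odds ratio for dependence 2.0 per within-sex SD lower; no other effect of sex; no other predictor. Sex was screened with Fisher's exact test at p < 0.05.

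| Result over the nine settings | Range |
|---|---|
| Studies in which the screen keeps sex | 4.5% to 7.0% |
| Odds ratio without sex in the model | 1.60 to 1.86 |
| Odds ratio with sex in the model | 1.99 to 2.03 |
| AUC without sex | 0.649 to 0.671 |
| AUC with sex | 0.681 to 0.685 |

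The Monte Carlo standard error at 5% is √(0.05 × 0.95 / 400) = 0.011, so the screen keeps sex about as often as its false-positive rate. On the log scale, ln 1.60 / ln 2 = 0.68 and ln 1.86 / ln 2 = 0.90, in line with step 3.

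**5. The sample size rule with sex fixed.** 100 + 50 × 9 = 550. If the planned BMI adjustment is counted as well, 100 + 50 × 10 = 600.

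**The case against.** The strongest reply is that the plan has a route for sex: it is collected and is a candidate under the covariate rule, and BMI is to be adjusted for as well. If dependence differs clearly by sex, the screen will tend to admit it. This stands, and it removes the worst case. It does not cover the case in steps 3 and 4, where sex matters only jointly with muscle size. The BMI adjustment is aimed at image quality and does not replace a sex term.

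Four other replies limit the point:

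- **Scaling.** The article states no scaling, but it does not say that raw values are used. That detail may sit in an analysis plan that is not shown. The predictor list and the covariate rule, however, are stated.
- **Reach of the limits.** They apply to BMI-relative thickness and DXA. Extending the argument to area and grip strength is by analogy.
- **Target.** The outcome is dependence, not sarcopenia. Whether absolute or sex-relative muscle predicts daily function better is an empirical question. The attenuation arises only if the sex-relative reading is the right one.
- **Size.** The gap between two cut-offs stands in for a gap between means. The formula is for one linear predictor, whereas the planned model is multivariable and logistic. Grip strength may carry part of the sex difference.

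A reader might infer that the muscle coefficients could reverse in sign, or that a score from this model would call women high-risk and men low-risk by body size. The documents do not support either reading. Reversal would need dependence to differ by sex, which is when the screen tends to bring sex in, and no figure in the article bears on how such a score would classify men and women.

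**Conclusion.** The point holds in a limited form. The main model does not secure a sex term, and the rule that could admit one tends to fail when dependence follows muscle relative to the own-sex level. The muscle slopes would then be attenuated to about 69% to 91% of the within-sex slope. In the simulated single-predictor model the AUC loss is about 0.01 to 0.03.

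These sizes rest on the assumed gap, standard deviations and sex mix, and would be smaller if grip strength carries part of the difference. The article does not contradict itself here: its limits are diagnostic background and do not define a model variable. This is a cheap improvement to a stated rule, not a flaw that invalidates the analysis.

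**What to change.** In Statistical analysis, name sex as a prespecified term in the main model, kept regardless of the univariate screen and exempt from the elastic net penalty. Place it alongside the BMI adjustment already planned. In step 4 one sex covariate was enough to restore the odds ratio, so sex-specific scores are not required. Standardising thickness, area and grip strength within sex, with means and standard deviations estimated in the training set, can be an optional sensitivity analysis.

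No new data are needed. The cost is one more parameter: by the article's own rule the sample would be 550, against the planned 500. State this in Sample size calculation rather than enrol more.

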We will follow these steps to perform model: a) delete variables with high multicollinearity that is, presenting a Variance Inflation Factor (VIF) highest than 5, b) check model assumptions, if residuals are not normality distributed, they will be transformed with log or Box-Cox transformation, if they present heteroskedasticity or residuals remain not normally distributed, robust bootstrap model will be applied, c) random split of data set into training (75%) and test (25%), c) train the model with cross validation (5-folders will be applied) and elastic net features selection (it combines lasso and ridge features selection), e) model performance will be assessed with confusion matrix, Receiver Operating Characteristic (ROC) curve and calculation of Area Under a Curve (AUC), sensitivity/specificity and F1 score and f) evaluation of variable importance.

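### Step b) of the model-building plan applies linear-model residual checks and a log/Box-Cox remedy to a logistic regression, so an undefined bootstrap fallback is triggered almost always, for reasons unrelated to misfit

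*Protocol article*

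**What the plan says.** The Statistical analysis section of the protocol article fixes the type of model, "A multivariate analysis will be performed with a machine learning model through principal analysis using logistic regression", and its outcome: "Model will be constructed with dichotomized Barthel index as dependent variable". The outcome is binary, with patients "dichotomized between dependent (BI < 60) and independent (BI > 60) patients". The predictors are "manual grip strength, EuroQoL-5D, NPRS, cross sectional area and thickness of the rectus femoris, STAI, TSK and BDI as explanatory variable". The Sample size calculation section treats this same model as the main analysis and derives the 500 participants from it.

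The same section then lists the model-building steps. Step a) removes collinear variables. Step b) checks the model assumptions. Its first instruction is "if residuals are not normality distributed, they will be transformed with log or Box-Cox transformation". Its second is "if they present heteroskedasticity or residuals remain not normally distributed, robust bootstrap model will be applied". The data split, cross-validation with elastic net, performance measures and variable importance follow.

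Step b) names neither a residual type nor a test. The only normality test in the section is given for quantitative variables, whose distribution "will be tested with the Kolmogorov-Smirnov test with Lilliefors correction". No regression with a continuous outcome is described to which step b) could apply instead.

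**The concern.** Normal residuals with constant variance are assumptions of the linear model. A logistic regression makes neither, and its residuals cannot be normal because the outcome is 0 or 1. The check can therefore fail when nothing is wrong with the model, and the prescribed transformation cannot make it pass.

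What is at stake is which model is finally reported. The fallback is named but not defined. The text does not say what is resampled, which estimator is used, or how it combines with the split, the five-fold cross-validation and the elastic net that follow. Analysts would have to carry out a rule that does not apply, or set it aside and depart from the published plan at their own discretion. This concerns the model on which the study is sized and which is meant to support intervention plans.

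**Working it through.** **Inputs from the protocol.** Binary Barthel outcome, logistic model, eight predictors, significance threshold 0.05 (Statistical analysis). The sample size rule is 100 + 50 × number of explanatory variables (Sample size calculation). The training share is 75%.

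**The plan's own figure.** 100 + 50 × 8 = 500, which reproduces the stated sample size. The training set is 0.75 × 500 = 375.

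**Residuals under a correct model.** Let p be the true probability for a given covariate pattern. The raw residual y − p equals 1 − p with probability p, and −p with probability 1 − p.
- Mean: p(1 − p) + (1 − p)(−p) = 0.
- Variance: p(1 − p)² + (1 − p)p² = p(1 − p).
- At p = 0.20 the residual is 0.80 or −0.20, with variance 0.20 × 0.80 = 0.16.
- At p = 0.50 it is 0.50 or −0.50, with variance 0.25.

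So the raw residual has two possible values given the covariates, and its variance changes with p as soon as any predictor has an effect. Both follow from a correct model.

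**The remedy.** The log, and Box-Cox without a shift, need positive values. Every participant with y = 0 has a negative raw residual; in the simulations below that was about 50–80% of participants. If the outcome is transformed instead, any function g maps {0, 1} to {g(0), g(1)}, which is still two values. If the predictors are transformed, the reason given does not apply, because logistic regression does not require normal predictors.

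**How often the check fails.** The protocol gives no prevalence or effect sizes, so these are assumptions shown over a range: prevalence of dependence 0.20, 0.35 and 0.50, and log-odds per SD of each predictor 0.1, 0.3 and 0.6. Correctly specified logistic models with eight standard-normal predictors were simulated at n = 500 and n = 375. That gives 2 × 3 × 3 = 18 settings, with 200 runs each and tests at 0.05. Using Lilliefors for the residuals is a further assumption.

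| Check on a correct model | Share of runs rejected |
|---|---|
| Lilliefors, deviance residuals | 100% in all 18 settings |
| Lilliefors, Pearson residuals | 99.5–100% |
| Lilliefors, raw residuals | 100% in 16 of 18 settings; 42.5% (n = 500) and 46.5% (n = 375) at prevalence 0.50 with log-odds 0.6 |
| Shapiro-Wilk, raw residuals, in those two settings | 98% and 88% |
| Lilliefors, deviance residuals after shifted Box-Cox | 99.5–100% |
| Breusch-Pagan on fitted p and p² | 70–100% |
| Breusch-Pagan on the eight predictors | 6–100% |
| Lilliefors, randomised quantile residuals | 1.5–6% |

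A separate simulation of the same kind again gave 100% for deviance and Pearson residuals. It gave about 33–38% for raw residuals at 50% prevalence with strong effects, and about 3–100% for Breusch-Pagan on the predictors. The range for raw residuals in that corner is therefore about 33–47%.

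The last row of the table is the contrast. A residual built for a binary outcome is rejected at about the nominal rate in the same correct models. The high rates elsewhere reflect the choice of check, not the fit.

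**The case against.** Four arguments can be made on the other side.

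**The check does not fail every time.** This stands. With raw residuals, a prevalence near 50% and strong effects, Lilliefors rejects in fewer than half of runs, and a variance test on the predictors can reject rarely. If no predictor had any effect, the raw residuals would have equal variance. A reader might infer that failure is certain. The supportable wording is almost always, with the dependence on residual type and test stated.

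**A correct model is not necessarily thrown away.** This also stands. A reader might infer that the rule discards the primary model. The fallback could, however, be a bootstrapped logistic regression, which keeps the model and changes only the interval estimates. Nothing in the text cancels the split, the cross-validation or the elastic net. Loss of the model, or bias in it, is not shown; ambiguity is.

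**Linearity, influence and calibration may be covered elsewhere.** This stands. A reader might conclude that they will go unchecked. Step b) opens with a general reference to assumptions, and a condensed article may leave such detail to an analysis plan that is not shown. Their absence is not part of this finding.

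**The whole matter may be a detail for the analysis plan.** This does not stand. The rule is stated, it is attached to the main model, and it is wrong for that model. A fuller document could replace it but would then contradict the published protocol.

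**Conclusion.** The point holds as a wrong rule in the text. Step b) tests a logistic regression against two assumptions that it does not make, and prescribes a transformation that cannot be carried out on negative residuals or cannot help a two-valued outcome. Under the assumed prevalences and effect sizes, correct models fail the normality check in essentially 100% of runs on deviance or Pearson residuals. On raw residuals they do so in 16 of 18 settings, and in about 33–47% of runs in the remaining corner. The undefined bootstrap fallback is therefore the near-certain route for reasons unrelated to misfit, and the final form of the primary model is left open.

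The algebra needs no assumption beyond a binary outcome and at least one predictor with an effect. The percentages rest on the assumed prevalences and log-odds, normal predictors, and the use of Lilliefors for residuals. The finding does not extend to the sample size, the choice of outcome or predictors, or the data collection.

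**What to change.** Delete the residual normality, heteroskedasticity and log/Box-Cox rule from step b), together with its bootstrap fallback. Replace it with checks suited to a binary outcome, such as linearity in the logit for the continuous predictors (by splines, fractional polynomials or an equivalent method) and influential observations. No single method needs to be imposed.

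The cost is revised wording and minor programming. The sample size stays at 500, because the deleted rule plays no part in 100 + 50 × 8. If the linearity check leads to non-linear terms being kept, the model gains a few parameters. As an illustration, one extra term each for grip strength, area and thickness gives 8 + 3 = 11 terms. The sample size rule counts explanatory variables; counting terms instead would give 100 + 50 × 11 = 650, so the plan should say how such terms are handled.

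A calibration slope and calibration plot on the test set in step e) would be an inexpensive optional addition, but that is a separate point.

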### Sample size calculation

The sample size was carried out based on the main objective and analysis of the study to evaluate which variables influence the level of dependence/independence through a multivariate logistic regression model, with Barthel index dichotomize as dependent variable, and manual grip strength, EuroQoL-5D, NPRS, cross sectional area and thickness of the rectus femoris, STAI, TSK and BDI as explanatory variable, for which a sample of 500 subjects was recommended according to Bujang et al. formula (100 + 50 × number of explanatory variables) and minimum sample size for logistic regression models [38–40].

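### The main objective asks which variables influence dependence, but the modelling steps are predictive and name no odds ratio, interval or test for the individual variables

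*Protocol article*

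**What the plan says.** In the Protocol article, Sample size calculation describes the "main objective and analysis of the study to evaluate which variables influence the level of dependence/independence through a multivariate logistic regression model". The named variables are "manual grip strength, EuroQoL-5D, NPRS, cross sectional area and thickness of the rectus femoris, STAI, TSK and BDI as explanatory variable", which makes eight.

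Statistical analysis sets a general level, "The level of significance will be set at *p* < 0.05". Its named uses there are the univariate comparisons of dependent with independent patients and, through them, the choice of baseline variables that the model adjusts for.

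The same section lists the modelling steps in order: removal of collinear variables, checks of assumptions, a random 75/25 split, training by 5-fold cross-validation with "elastic net features selection (it combines lasso and ridge features selection", performance measures (confusion matrix, ROC curve and AUC, sensitivity and specificity, F1), and an assessment of how important each variable is. It gives a trained model as the goal. Implications and limitations also describes the model as one that predicts dependence.

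**The concern.** One procedure is meant to serve two purposes and suits only one of them. Cross-validation chooses the penalty that predicts best. It sets no limit on how often a variable unrelated to dependence stays in the model. The ridge part of the penalty tends to keep more variables, and an importance ranking always puts some variable first. The retained coefficients are shrunk and selected, so ordinary p-values and confidence intervals do not apply to them.

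If the report says that rectus femoris area or thickness was selected, readers may take this as evidence that it matters for dependence. It would be weak evidence if irrelevant variables are often selected too. The study's case rests on what ultrasound adds to frailty assessment, so this is a conclusion that readers will look for.

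**Working it through.** **The plan's own figure.** The rule is "100 + 50 × number of explanatory variables". With eight variables, 100 + 50 × 8 = 500, which matches the stated sample. The plan states no error rate for selection, so there is none to reproduce.

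**Inputs from the article.** Eight explanatory variables; 500 patients; training set 0.75 × 500 = 375; 5-fold cross-validation; elastic net; level 0.05 (taken as two-sided).

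**Inputs assumed, because the article does not give them.** Standardised predictors with pairwise correlation 0 or 0.3; about 40% dependent (20% and 50% also tried); log-odds ratio 0.5 per SD for each true predictor, that is exp(0.5) = 1.65 (0.3 also tried); 0 to 7 true predictors out of eight; mixing weight 0.5 or 1 (0.1 also tried). Adjustment covariates were left out. At correlation 0.3 the variance inflation factor is 1/(1 − 7 × 0.3²/(1 + 6 × 0.3)) = 1/(1 − 0.225) = 1.29, so the plan's deletion threshold of 5 would remove nothing.

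**Method.** Elastic-net logistic regression with the penalty at minimum cross-validated deviance or by the one-standard-error (one-SE) rule, compared with two-sided Wald tests at 0.05 in the unpenalised eight-variable model. There were 1000 data sets per scenario, so the simulation error of a rate near 50% is √(0.25/1000) = 1.6 percentage points.

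Results for n = 375, mixing 0.5 and 40% dependent. Each cell gives the percentage of samples that keep at least one irrelevant variable / the percentage that keep any given one.

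| True predictors | Correlation | Elastic net, CV minimum | Elastic net, one-SE | Wald p < 0.05 |
|---|---|---|---|---|
| 0 | 0 | 31 / 12 | 2 / 1 | 33 / 5 |
| 1 | 0 | 79 / 34 | 14 / 3 | 28 / 5 |
| 4 | 0 | 97 / 66 | 42 / 15 | 18 / 5 |
| 7 | 0 | 82 / 82 | 29 / 29 | 4 / 4 |
| 0 | 0.3 | 33 / 12 | 2 / 1 | 34 / 6 |
| 1 | 0.3 | 85 / 35 | 21 / 5 | 29 / 5 |
| 4 | 0.3 | 96 / 59 | 75 / 30 | 16 / 4 |
| 7 | 0.3 | 69 / 69 | 46 / 46 | 4 / 4 |

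**Range at the CV minimum.** Over all runs with mixing 0.5 or 1 and at least one true predictor: 62–97% for at least one irrelevant variable, 26–82% for each. With four true predictors and correlation 0.3, changing the share dependent to 20% or 50% gives 96% and 60%; the weaker effect (0.3) gives 93% and 52%; mixing 0.1 gives 100% and 86%.

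**Sensitivity to tuning.** The one-SE rule at mixing 0.5 gave about 4–24% per variable in scenarios with one, three or four true predictors of unequal strength. The wider grid above, with up to seven equal predictors, spans 3–46%. At mixing 0.1 the one-SE rule kept at least one irrelevant variable in 100%. Choosing the mixing weight by AUC gave 32–36% for at least one irrelevant variable with one true predictor, but 87–90% with none.

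**Like-for-like comparison.** Independent tests at 0.05 would give 1 − 0.95⁴ = 18.5% for at least one of four irrelevant variables and 1 − 0.95⁸ = 33.7% for at least one of eight. The simulated Wald figures at 40% dependent are 16–18% and 33–34%.

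**What selection tells the reader.** Take four true predictors and correlation 0.3. At n = 375 the elastic net keeps a true predictor in 100% of samples and an irrelevant one in 59%, a ratio of 1.00/0.59 = 1.7. The Wald test on all 500 patients keeps them in 98% and 5%, a ratio of 0.98/0.05 = 19.6. The split is not the cause: the elastic net on 500 patients still keeps each irrelevant variable in 61%.

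**The case against.** The strongest reply is that the article never says that a selected variable will be declared influential. It says that the objective is addressed through a multivariate logistic regression, and it prefers that model partly because it is easy to interpret. Coefficients and intervals may well be reported under a full analysis plan that is not shown. The stated goal of a trained model is well served by an elastic net with a held-out test set. Much of this stands: the link from selection to influence is inferred from the listed steps.

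A reader might also infer that the 0.05 level goes unused. The text does not support that, since the level governs the univariate tests and, through them, the adjustment covariates. Nor is it right that irrelevant variables are kept in most samples whatever the tuning. The one-SE rule often gives far lower rates, and with no true predictor about 30% of samples keep any variable at mixing 0.5 or 1, no worse than eight Wald tests. Unpenalised tests without multiplicity control will also name an irrelevant variable fairly often.

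What the reply does not remove is the mismatch. The article fixes the steps one by one, and none of those listed provides inference on individual variables for the objective that it calls main.

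**Conclusion.** The point holds as a mismatch between the explanatory objective and a predictive set of steps, and it should be fixed before analysis. On the usual choice of penalty (the cross-validation minimum), with mixing weight 0.5 or 1 and some true predictors, selection would keep at least one irrelevant variable in about 62–97% of samples and each one in about 26–82%. The unpenalised tests keep each in about 4–6%, and at least one of four in about 16–18%. These sizes depend on effects, prevalence, correlations and tuning that the article does not give, so they illustrate the problem and do not forecast this study's error rate.

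The documents do not support the stronger reading that the study will draw its main conclusion by declaring selected variables influential. They leave open how influence will be judged. The sample size of 500 is unaffected.

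**What to change.** In Statistical analysis, separate the two purposes.

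- **Explanatory objective.** Fit the pre-specified eight-variable logistic model, unpenalised or with Firth's correction, to all 500 patients. Report every odds ratio with its 95% confidence interval and p-value, and base the conclusion on these. State that eight tests are made without multiplicity control.
- **Prediction.** Keep the elastic net, the 5-fold cross-validation and the 75/25 split. State that selection and importance rank are descriptive and are not evidence that a variable influences dependence.

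The cost is one extra model on data already collected and a few sentences of text. Fewer variables may be declared influential. In the scenario with four true predictors, correlation 0.3 and odds ratio 1.65 per SD, the model on 500 patients still detects a true predictor in 98% of samples. Power is lower for weaker effects: at a log-odds ratio of 0.3 and n = 375 it is 64%.
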